### Withdrawals

Participants may withdraw from the study due to illness or personal reasons. They will be made aware (via the information sheet and consent form) that withdrawal from the study will not affect their future care, and that data collected to date will still be used in the final analysis. Volunteers who are not randomised because they fail eligibility criteria at baseline will be replaced, but participants who withdraw from the trial for any reason will not be replaced.

### Statistical methods

Data will be entered into an SPSS (latest version) computer data-base using the registration number to identify the participant. All paper data will be stored in a secure locked cabinet, and all computer data will be stored on a secure server.

Baseline data will be analysed to describe the characteristics of the participants and to check for significant imbalance between the three groups. All outcomes will be analysed at each follow up assessment point (six, 24 and 36 weeks), and specific *a priori *hypotheses will be tested reflecting the outcomes that we expect to identify at the different stages. In each case a two sided test will be used. It is expected that t tests will be conducted to compare groups, unless any obvious deviations from t test assumptions are found in the outcomes, in which case the non - parametric Mann Whitney U test will be used.

In order to identify short term benefits, participants in the specialist rehabilitation groups (A and B) will be compared with participants receiving information pack only (group C) at six weeks. The null hypotheses will be tested, that there are no differences between the groups, with respect to change in patient disability, mobility and psychological wellbeing, and in carer strain. These hypotheses will be tested using each participant's change score from baseline (week 0) to week 6.

In order to identify medium term benefits, comparisons will be made at 24 weeks between pairs of treatment groups (Group A vs. Group B; Group A vs. Group C; Group B vs. Group C). The null hypotheses will be tested, that there are no differences between the groups with respect to change in patient disability, mobility, falls, speech, activities of daily living, social activities, psychological wellbeing, health related quality of life and use of health and social care services, and in carer strain, social activities and health related quality of life. These hypotheses will be tested using each participant's change score from baseline (week 0) to week 24.

In order to show loss or maintenance of benefit resulting from specialist rehabilitation, Group A (no ongoing support weeks 7 and 24) will be compared with Group B (ongoing support weeks 7 to 24) using the hypotheses in the medium term analysis and each participant's change score from week 6 to week 24.

In order to identify longer term benefits, comparisons will be made at 36 weeks between pairs of treatment groups (Group A vs. Group B; Group A vs. Group C; Group B vs. Group C). The null hypotheses will be tested, that there are no differences between the groups with respect to change in patient disability, mobility, falls, speech, activities of daily living, social activities, psychological wellbeing, health related quality of life and use of health and social care services, and in carer strain, social activities and health related quality of life. These hypotheses will be tested using each participant's change score from baseline (week 0) to week 36.

An additional exploratory analysis will be performed using each participants change score for the above outcomes between week 24 and week 36. This is the follow-up period, and this analysis will provide evidence of trends in each group, and difference between groups, after all interventions cease in week 24.

It is recognised that multiple statistical tests are being undertaken, but no adjustments will be needed for multiple testing because *a priori *hypotheses have been stipulated, and the selective reporting of significant results will be avoided. Any additional exploratory (hypothesis generating) data analyses will make allowance for multiple testing in the usual way (Bonferroni).

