### Registration and randomisation

After consent and baseline data have been collected, eligible volunteers will be given a unique registration number by the project administrator and randomised to either: Group A - specialist rehabilitation, Group B - specialist rehabilitation and ongoing care assistant support, or Group C - usual care, control group. A separate randomisation sequence will be prepared by the study statistician prior to the commencement of the study for patients without live-in carers and for patients with live-in carers. In each instance, blocked randomisation will be used to formulate the sequence involving the three comparison groups. A non-computerised random number generator will create random permuted blocks of size three with an equal allocation ratio (with any of the six different group sequences being equally possible). The project administrator will inform: all participants of the group to which they have been randomised; the MDT of participants randomised to either of the treatment arms; the GPs of all participants about their involvement in the trial and the group to which they have been randomised. Since the project administrator will not be involved in the process of consenting volunteers into the study, and randomisation of eligible participants will be conducted in chronological order of study entry, no attempt will be made to conceal from the project administrator the next group to which the next patient would be allocated. However, only the project administrator and the study statistician will have access to each randomisation sequence.

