The economic analysis will evaluate the costs of the intervention in relation to all patient and carer consequences/outcomes [64]. In addition, a cost-effectiveness analysis will be conducted, using standard techniques of economic appraisal [65]. Mean differences between groups (Group A (specialist rehabilitation only) vs. group C (normal care controls); Group B (rehabilitation with ongoing support) vs. Group A) in the primary outcome measures (disability score for patients, carer strain) and in QALYs (patients only) adjusted for baseline values in an analysis of covariance, will be used to measure effectiveness. If statistically significant differences between groups are found, incremental cost-effectiveness ratios will be calculated to show the extra cost incurred per unit of therapeutic gain/QALY gain. Secondary cost-effectiveness analyses will be conducted using other outcomes as measures of effectiveness.

The impact of uncertainties in the estimation of costs and outcome variables will be explored using one way and probabilistic sensitivity analysis. Bootstrap methods will be used to represent uncertainty of estimates, either for constructing confidence intervals or probability curves. Sensitivity analysis will also investigate the cost-effectiveness of the interventions for people with different levels of disability at baseline.

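### The clinical analysis tests change scores without covariates, while the economic evaluation uses baseline-adjusted ANCOVA on the same two primary outcomes; ANCOVA should serve both

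*Protocol article*

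**What the plan says.** All references are to the protocol article.

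- **Test.** Statistical methods: "It is expected that t tests will be conducted to compare groups, unless any obvious deviations from t test assumptions are found". If they are, the comparison moves to a Mann-Whitney test. No covariate is named.
- **Variable analysed.** The same section fixes the change score. For the short-term comparison (A and B together against C): "These hypotheses will be tested using each participant's change score from baseline (week 0) to week 6". For the pairwise medium-term comparisons: "These hypotheses will be tested using each participant's change score from baseline (week 0) to week 24". The week 36 comparisons use change from baseline in the same way, and the A vs B maintenance comparison uses change from week 6 to week 24.
- **Baseline.** Consent and baseline data collection has the trial's outcome measures recorded at the baseline visit.
- **Stratification.** Registration and randomisation: "A separate randomisation sequence will be prepared by the study statistician prior to the commencement of the study", one for patients with a live-in carer and one for patients without.
- **Economic evaluation.** Mean differences for A vs C and B vs A in disability score, carer strain and QALYs, "adjusted for baseline values in an analysis of covariance, will be used to measure effectiveness". Incremental cost-effectiveness ratios (ICERs) follow only if differences are statistically significant; the section does not say which test decides that.

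**The concern.** For both primary outcomes, and for two of the three pairwise contrasts, the article prescribes two estimators: a change-score t test (or a rank test) in the clinical analysis and ANCOVA in the economic one. Unless baseline means happen to coincide, their estimates and p values can differ. Because the ICERs hang on significance, a reader cannot tell which result governs if one method crosses 5% and the other does not. If the clinical analysis falls back to Mann-Whitney, it supplies no mean difference to set beside the economic one.

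The clinical method is also the less precise of the two. Subtracting the whole baseline score over-corrects whenever the correlation between baseline and follow-up is below 1 (equal SDs), so a chance baseline difference passes into the estimate. The article plans a check for baseline imbalance but attaches no analysis to its result. The live-in-carer factor that shaped the patient randomisation appears in none of the planned tests.

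**Working it through.** **Inputs.** Sample size calculations: patient difference 1.25 with SD 2.5; carer difference 0.535 with SD 1.07; two-sided 5%, power 80%, 64 per group; 90 patients per group recruited, 10% loss; 79% with a live-in carer. The correlation r between baseline and follow-up is not given; 0.3 to 0.9 is assumed.

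**The plan's own figure.** Both standardised differences are 0.5 (1.25/2.5 and 0.535/1.07). The normal formula gives 63 per group, the t-based solution 63.77, so 64. Power of the t test at 64 is 80.1%. The stated figure reproduces.

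**Numbers available for analysis.** Patients: 90 × 0.90 = 81 per group. Carers: 90 × 0.79 = 71 per group; the same 10% loss would leave 71.1 × 0.90 = 64. The figures at 64 therefore describe the carer analysis and the patient minimum; those at 81 describe patients as planned.

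**Variance.** With equal SD s at both times:
- change score: 2s²(1 − r)
- ANCOVA: s²(1 − r²)
- ratio ANCOVA/change: (1 + r)/2, which is 0.65, 0.75, 0.85 and 0.95 at r = 0.3, 0.5, 0.7 and 0.9. It is below 1 for every r < 1.

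**Power if 2.5 is the SD of change.** ANCOVA SD = 2.5 × √((1 + r)/2).

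| r | ANCOVA SD | power at 64 (change score 80%) | power at 81 (change score 88.5%) |
|---|---|---|---|
| 0.3 | 2.02 | 94% | 97.5% |
| 0.5 | 2.17 | 90% | 95.5% |
| 0.7 | 2.30 | 86% | 92.9% |
| 0.9 | 2.44 | 82% | 90.1% |

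**Power if 2.5 is the SD of a single score.** Change SD = 2.5 × √(2(1 − r)); ANCOVA SD = 2.5 × √(1 − r²).

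| r | change SD | ANCOVA SD | at 64: change / ANCOVA | at 81: change / ANCOVA |
|---|---|---|---|---|
| 0.3 | 2.96 | 2.39 | 66% / 84% | 76% / 91% |
| 0.5 | 2.50 | 2.17 | 80% / 90% | 88.5% / 95.5% |
| 0.7 | 1.94 | 1.79 | 95% / 98% | 98% / 99% |

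The article does not say which SD it means. At 64 per group its 80% fits the planned test only if 2.5 is a change SD, or a single-score SD with r of about 0.5 or more. Carers have the same standardised difference, so the same powers apply with 1.07 in place of 2.5.

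**Chance imbalance.** Given a baseline difference D between groups, the expected follow-up difference is the effect plus rD, so the change-score estimate is off by (1 − r)D in size. For D = 0.2 SD, which is 0.5 points if 2.5 is a single-score SD, that is 0.35, 0.25 and 0.15 points at r = 0.3, 0.5 and 0.7, against a target of 1.25. ANCOVA removes this shift.

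**The switch to Mann-Whitney.** Simulation under the null, 64 per group, 10,000 runs: a fixed Shapiro-Wilk rule gave type I error of about 4.7% for normal and for skewed data. Free choice of the smaller p value gave 5.6% and 6.3%.

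**The case against.** The strongest reply is that nothing here is an invalid analysis. Under randomisation the change-score t test is unbiased on average and holds its size, and baseline does enter through the subtraction. That stands. A reader might infer from the word unadjusted that the clinical results would be biased; the documents do not support this. The fault is lost precision, sensitivity to the imbalance that happens to occur, and inconsistency with the economic section.

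A reader might also infer that the trial is underpowered, from the 66% in the table. That figure needs three things together: 2.5 as a single-score SD, r as low as 0.3, and only 64 per group. With the 81 patients planned it is 76%, and at r = 0.7 the change-score test has 95% even at 64. With no r in the document, only the full range can be reported.

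A third inference is that the Mann-Whitney fallback leaves the choice of test open to the results. The fallback is stated in advance, the Blinding section withholds group identifiers from the statistician, and the simulated inflation is small. A numerical criterion for departure from assumptions is detail an article may leave to the analysis plan. What remains is that a rank test yields no mean difference to match the economic estimate.

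It would also be too strong to say that the trial will publish two effects for one contrast. The two can differ, for A vs C and B vs A on the primary outcomes. The economic section names no time point and covers neither B vs C nor the pooled week 6 comparison. The repeated measures analysis mentioned under Missing data may carry covariates in a plan not shown, but that would not reconcile the two methods the article states.

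Finally, the carer stratum is constant among carers and cannot enter the carer-strain model, so the point about ignoring it concerns patient outcomes only. No loss from omitting it has been quantified.

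**Conclusion.** The point holds as one of efficiency and consistency, and the change should be made. For comparisons from baseline, ANCOVA reduces the variance of the contrast by 5% to 35% over r from 0.9 to 0.3, assuming equal SDs at both times. If 2.5 is a change SD, that is 2 to 14 percentage points of power at 64 per group and about 2 to 9 at 81. If it is a single-score SD, the gain at 64 is 18 points at r = 0.3, 10 at r = 0.5 and about 2 at r = 0.7. The value of r and the meaning of the planning SD are both unknown from the document, so the size of the gain is a range. The inconsistency with the economic section, including the unspecified test behind the ICER condition, depends on neither. The stated sample size is not in error.

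**What to change.** 1. For comparisons from baseline at weeks 6, 24 and 36, make ANCOVA the primary clinical analysis: follow-up score on group and baseline score. Add the live-in-carer stratum for patient outcomes only.
2. Deal with non-normality by robust or bootstrap standard errors, and keep Mann-Whitney as a sensitivity analysis.
3. Use these same estimates in the economic evaluation, and state that they decide the significance condition for the ICERs if that condition is kept.
4. The week 6 to 24 maintenance comparison may stay as a change score, since within-person change from week 6 answers that question directly; conditioning on week 6 instead would be a choice, not a correction.
5. State whether the SDs of 2.5 and 1.07 are for change or for single scores.

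The cost is analysis wording. Every covariate is already collected, and no participants, visits or instruments are added.

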4. Assess the costs of the specialist rehabilitation intervention, and of the ongoing care assistant support, and calculate relative cost-effectiveness, including consideration of savings from service use offsets;

5. Investigate the acceptability of the new service delivery models (specialist domiciliary rehabilitation with and without ongoing support from trained care assistants) from the perspectives of all stakeholders including commissioners, MDT members, care assistants, service managers, patients and family carers;

6. Deliver guidance for commissioners, providers and policy makers about the acceptability, clinical and cost-effectiveness of different models of specialist neurological rehabilitation.

The **hypotheses **are that:

1. A package of domiciliary multidisciplinary specialist rehabilitation will benefit:

a. People with Parkinson's in terms of maintaining mobility and independence (primary outcome for patients), and improving wellbeing and health-related quality of life,

b. Family carers in terms of reduced strain (primary outcome for carers), and improved health-related quality of life, and

c. Society through reduced use of other health and social care services, including hospitalisations and admissions to long term care.

2. The addition of four months of ongoing support from trained care assistants will help to maintain the benefits of the specialist team rehabilitation, and avoid the fading of effects that typically accompanies the withdrawal of input.

3. The intervention will be acceptable to major stakeholders, and that barriers and facilitators to wider implementation will be identified.

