## Design/Methods

### Design

A pragmatic three parallel group randomised controlled trial. People with Parkinson's in group A will be assessed and managed by a specialist MDT according to a care plan that is agreed amongst the professionals and with the patient and carer. Group B will additionally receive ongoing support for four months from a trained care assistant. Group C will receive normal care (no coordinated MDT care planning or ongoing support). Follow up will be for six months to determine the impact and relative cost-effectiveness of the two interventions. Qualitative interviews will be undertaken with providers (MDT members, care assistants), service commissioners, and patients and carers in groups A and B, to gain feedback about the acceptability of the interventions. The CONSORT diagram [42] summarises the design (Figure 1).

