### Outcome measures

Participants in all groups will be assessed in their homes by a research nurse, according to the schedule used in the day hospital trial, at weeks 6 (after the rehabilitation intervention), 24 (four months after the end rehabilitation, coinciding with the end ongoing support for Group B), and 36 (for final follow up). Validated instruments which reflect the needs of participants (e.g. functional outcomes, quality of life) and service commissioners (e.g. service use), and which have been found sensitive in previous rehabilitation studies undertaken by the research team [10-13] have been selected to measure outcomes (Table 1).

**Table 1 T1:** Trial outcome measures and instruments: baseline, 6, 24 and 36 weeks

Participant	Outcome measure	Instrument
Person with Parkinson's	Parkinson's disability/general activities	Self Assessment Parkinson's Disease Disability Scale [46] (PRIMARY OUTCOME)
	
	Parkinson's specific	Parkinson's Disease Questionnaire [47]
		
		Non Motor Symptom Questionnaire [48]
	
	Mobility	Posture and gait items from the Unified Parkinson's Disease Rating Scale [49]
		
		Timed up and go [50]
	
	Falls	Self report
	
	Speech	Single speech item from the Unified Parkinson's Disease Rating Scale [49]
		
		Abridged Emerson and Enderby Screening Assessment Rating Scale [51]
		
		Frenchay Dysarthria Summary [52]
		
		Speech self report questionnaire [10-12]
	
	Pain	Visual analogue scale [53]
	
	Generic health related quality of life/QALYs	Euro Qol 5D, with utility index for calculation of quality adjusted life years (QALYs) [54]
	
	Self efficacy	Self efficacy scale [55]
	
	Health and social care utilisation	Customised proforma and patient records

Live-in carer	Carer strain	Modified caregiver strain index [56] (PRIMARY OUTCOME)
	
	General health	General health questionnaire - 12 [57]

Both	Activities of daily living	Barthel ADL index [58]
	
	Social activities	Frenchay Activities index [59]
	
	Psychological wellbeing	Hospital Anxiety and Depression Scale [60]
		
		Yale single item depression screening tool [61]
	
	Generic health related quality of life	Short form - 36 Health Survey [62]

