### Sample size calculations

Patient sample size calculations were based on detecting clinically meaningful differences in the primary patient outcome measure. Carer sample sizes reflect the findings of our previous work that suggest that 79% of people with Parkinson's have a carer [10].

We will recruit 270 people with Parkinson's over a 12 month period across the three areas, 90 of whom will be randomly allocated to each of the three groups. This calculation is based on the numbers of people with Parkinson's needed to detect differences between groups in patient primary outcome measure score.

Assuming a similar level of variation in Self Assessment Parkinson's Disease Disability Scale [46] to the day hospital trial [11], in order to detect a difference in the disability score of 1.25 (assuming SD = 2.5, size = 5%, power = 80% and a 2 sided test), 64 subjects with Parkinson's disease are needed in each of the three groups.

Assuming a similar level of variation in Carer Strain Index [56] to the day hospital trial [11], in order to detect a difference in the Carer Strain Index of 0.535 (assuming SD = 1.07, size = 5%, power = 80% and a 2 sided test), 64 carers are needed in each of the three groups. In the previous study, 79% of community dwelling people with Parkinson's had a live-in carer [10]. Thus, if we have 64 carers per group, this will necessitate 246 [(64*3)/0.79 = 243.04] Parkinson's subjects, i.e 82 per group.

In the previous day hospital trial the loss to follow-up/non completion/missing data rate between recruitment and six month assessments was 26%. However, in this trial, participants attended the day hospital for treatment (six visits) and research assessments (four visits), and difficulties with transport and inter-current illness accounted for missing data and drop-out. We expect less attrition in the SPIRiTT trial because participants will receive both treatment and the research assessments in their own homes, at times convenient to them.

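### Each primary outcome is tested eight times at 5% with no primary week or contrast, and the stated reasons for making no multiplicity adjustment do not control the false-positive rate

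*Protocol article*

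**What the plan says.** The abstract and Table 1 of the protocol article name two primary outcomes: patient disability (a self-assessed Parkinson's disability scale) and carer strain (the modified caregiver strain index). Table 1 lists its instruments for baseline and all three follow-ups and marks no visit as primary.

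On timing, Statistical methods says: "All outcomes will be analysed at each follow up assessment point (six, 24 and 36 weeks". It then sets two-sided tests of change scores in four steps:

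- week 6: A and B against C;
- week 24: A vs B, A vs C and B vs C;
- weeks 6 to 24: A vs B;
- week 36: A vs B, A vs C and B vs C.

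Analysis of the change from week 24 to week 36 is labelled exploratory. On multiplicity the section says: "It is recognised that multiple statistical tests are being undertaken, but no adjustments will be needed for multiple testing". It gives two reasons, pre-stated hypotheses and avoidance of selective reporting, and keeps Bonferroni for additional exploratory analyses.

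Sample size calculations takes one two-group difference per primary outcome. For patients, "in order to detect a difference in the disability score of 1.25" is followed by "assuming SD = 2.5, size = 5%, power = 80% and a 2 sided test), 64 subjects with Parkinson's disease are needed" in each group. For carers it is a "difference in the Carer Strain Index of 0.535 (assuming SD = 1.07, size = 5%, power = 80% and a 2 sided test", again with 64 per group. It names neither the pair of groups nor the week.

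Two other statements bear on the point. The Design section says: "Follow up will be for six months to determine the impact and relative cost-effectiveness of the two interventions", while Outcome measures sets the last assessment at week "36 (for final follow up". Hypothesis 1a, in the Background, speaks of "maintaining mobility and independence (primary outcome for patients".

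**The concern.** Stating hypotheses in advance stops them being chosen after the data are seen. Full reporting stops results being picked out. Neither changes the chance that at least one of several 5% tests is significant when nothing works. That chance depends on how many tests could support a claim and how they are correlated.

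Here nothing ranks the tests. A difference at week 6 only, in one pair at week 24, or in one pair at week 36 would each be a significant result on a primary outcome, and the protocol does not say which would make the trial positive. The 80% power is promised for a comparison that is never identified. The Economic evaluation section makes cost-effectiveness ratios conditional on statistically significant group differences, also without naming a week, so the ambiguity carries into that analysis.

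This is a rule the protocol states, with a reason that does not support it. It is therefore not a detail that could simply be left to an analysis plan.

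**Working it through.** **1. The plan's own figure.** Both primary outcomes are sized for a standardised difference of 0.5: 1.25/2.5 = 0.5 and 0.535/1.07 = 0.5. With n per group = 2(z₀.₉₇₅ + z₀.₈₀)²/d² = 2(1.960 + 0.842)²/0.25 = 62.8, the normal approximation gives 63. The exact t test gives 63.8, so 64, as stated. Power of the t test at 64 per group is 80%. The 64 is thus the size for one unadjusted two-group test.

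The inflation also reproduces: 64 × 3/0.79 = 243.04 and 243.04/0.90 = 270.04, or 90 per group. After 10% loss that leaves 81 patients per group and 81 × 0.79 = 64 carers per group.

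**2. Count of tests per primary outcome.**

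| Analysis | Contrasts | Tests |
|---|---|---|
| Change to week 6 | A and B (pooled) vs C | 1 |
| Change to week 24 | three pairs | 3 |
| Change from week 6 to week 24 | A vs B | 1 |
| Change to week 36 | three pairs | 3 |
| Total | | 8 |

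The count is conservative. It reads week 6 as one pooled contrast and leaves out the exploratory week 24 to 36 analysis. Reading week 6 as A vs C and B vs C separately gives 9.

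**3. False-positive rate under no effect.** Eight independent tests would give 1 − 0.95⁸ = 34%. The tests are correlated, so this is too high. I simulated them by normal theory, with three equal groups, equal variances at all visits and the same correlation between any two visits (values 0.3, 0.5, 0.7 and 0.9 tried):

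- three week 24 pairs alone: about 12%;
- all eight tests on one primary outcome: about 27%;
- nine tests, with week 6 split: about 29%.

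The results hardly move with the assumed correlation. With equal correlation between visits, two changes from the same baseline correlate at 0.5 whatever the visit correlation is.

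**4. Cost of keeping all three pairs primary at one week.** The procedure is a global three-group F test at 5%, then each pair at 5% only if the global test is significant. Under no effect the simulated chance of any claim on one outcome is 5.0%. Power for B vs C, true difference 0.5 SD:

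| | Unadjusted | Gated, A as effective as B | Gated, A half as effective |
|---|---|---|---|
| Patients, 81 per group | 88.5% | 86% | 81% |
| Carers, 64 per group | 80% | 76% | 70% |

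Patients stay above 80% in both cases. Carers fall below it in both.

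**The case against.** The strongest defence is that the trial asks staged and distinct questions (short-term benefit, medium-term benefit, maintenance, longer-term benefit) that follow from hypotheses 1 and 2. Leaving pre-stated comparisons unadjusted while correcting unplanned ones is a recognised, if debated, position. The protocol also promises to avoid selective reporting, and nowhere says that any one significant test would count as success.

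Part of this stands. Separate questions can justify separate 5% tests, for example A vs C and B vs C at one visit, and full reporting lets a reader judge the whole pattern. It does not cover repeating all three pairs at two visits, with two further contrasts, on the same outcome and with none designated primary. The debated position also needs a defined main question, and that is missing.

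Four stronger readings are tempting, and the documents do not support them:

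- **One family of 16 tests.** Pooling both primary outcomes gives a chance of about 44 to 47% under the same model with a patient–carer correlation of 0 to 0.5. But Outcome measures says that patients and carers are analysed separately, so eight tests and about 27% per outcome is the fair family.
- **A total over all outcomes.** Any such count depends on how instruments are assigned to the listed domains, which the protocol does not set out.
- **Six months is an error for 36 weeks.** Week 36 is about 8.3 months and week 24 about 5.5. The schedule is taken from the day hospital trial, and the sample size section speaks of that trial's six-month assessments. Six months may therefore mean the week 24 visit. The text shows a conflict, not which figure is wrong.
- **The patient primary outcome is undefined.** The abstract and Table 1 agree on disability. Only the wording of hypothesis 1a departs from them.

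**Conclusion.** The point holds per primary outcome. The protocol sets eight two-sided 5% tests on each, names no primary week or contrast, and justifies making no adjustment with two reasons that do not control error. The chance of at least one false-positive result is about 27% per primary outcome, more than five times the nominal 5%, and about 12% from the week 24 pairs alone. These figures assume no effect at any visit, equal variances and equal correlation between visits. They describe the chance of any significant result. They are the chance of a false claim only if any of the eight may carry one, which the text neither says nor rules out.

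The sample size arithmetic is sound for a single comparison. The fault is that this comparison is not identified. The conflicts over six months and over hypothesis 1a are separate matters of wording, and neither is needed for the conclusion.

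**What to change.** 1. Delete the statement that no adjustments are needed, together with its rationale.
2. Name one primary time point (week 24, when Group B's support ends, is an example) and one primary contrast for each primary outcome. This keeps the planned 5% size per outcome and 80% power at 64 per group. It changes wording only.
3. Label all other contrasts, weeks and outcomes secondary, and report them with confidence intervals.
4. If all three pairs are to stay primary at the chosen week, use the global three-group test at 5% and then the pairs at 5%. Say that this controls error within each outcome and not jointly: over two independent outcomes the chance of any false claim could reach 1 − 0.95² = 9.75%. Restate the carer power, which falls from 80% to about 76%, or 70% if A has half of B's effect. Patient power falls from about 88.5% to 86%, or 81%.
5. Separately, reconcile the six-month follow-up in the abstract and Design section with the week 36 final assessment, and make hypothesis 1a agree with the disability scale that the abstract and Table 1 name as primary.

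The choice of week and contrast should be made and dated before any outcome data are compared by group.
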